### Sample size estimation

2.3

This study is a randomized controlled trial, where the intervention group will receive the mobile health intervention and the standard care group will receive standard care. The outcome measure is the prenatal diagnosis demand. Based on previous randomized controlled trials related to willingness to undergo screening for related diseases, the intervention group’s demand proportion is 53.4%, and the standard care group’s is 34%, showing an increase of approximately 19.4% (28). We predict that the mobile health intervention based on the Behavior Change Wheel theory and Family Health Theory may lead to a doubling of the demand proportion (38.8%), reaching 72.8% (29). The expected demand proportion for the intervention group is 72.8%, and for the standard care group is 34%. Using a two-sided test with α = 0.05, β = 0.2, and power (1-β) = 80%, the sample size ratio between the two groups is 1:1. After using the PASS software (version 2021) to calculate the relevant values, it was determined that 23 participants per group would be required. Considering a 20% dropout rate, the final sample size for each group is 29 participants, for a total of 58 participants.

### Randomization and blinding

2.4

In this study, randomization was conducted using Excel software to ensure unbiased group allocation (**Figure 5**). The procedure is as follows: First, a new worksheet was created in Excel, with numbers from 1 to N in column A (where N is the total number of subjects), representing the subject identifiers. In column B, the formula =RAND() was used to generate a random number between 0 and 1 for each subject. Then, to prevent any changes to the random numbers, they were copied and pasted as “values.” After that, the subjects were sorted based on the random numbers in column B, and group allocations were made according to the sorted order.

**Figure 5 f5:**
[figure not shown]
The process of randomization.

During group allocation, the order after sorting determines each subject’s group. Specifically, subjects in odd-numbered positions in the sorted order were allocated to the standard care group, while those in even-numbered positions were allocated to the intervention group. It should be noted that the subject identifiers remain in column A, but the actual group assignment is based on the sorted order in column B.

To ensure blinding, a single-blind design was adopted, where subjects were unaware of which group they were assigned to, but the evaluators were not blinded. To implement allocation concealment, the envelope method was used for group allocation. The procedure is as follows: Sufficient opaque envelopes were prepared, each marked with a unique identifier number corresponding to the subject’s identifier in column A of the Excel sheet. A small slip of paper with the group allocation information (Intervention Group and Standard Care Group) was placed inside each envelope. This allocation information corresponds to the envelope number, which matches the subject’s identifier in column A, ensuring that the envelope received by each subject corresponds to their assigned group based on the randomization process. The envelopes were then sealed.

After enrollment, subjects received an envelope in sequential order based on their subject identifier in column A. Each subject opened their envelope independently to reveal their group assignment. The distribution and opening of the envelopes were supervised by a designated person, and the process was recorded. All unused envelopes were securely stored to maintain the integrity of allocation concealment and the single-blind design.

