### Design

2.1

This study is a single-blind, interventional randomized controlled trial conducted at the Inner Mongolia Maternity and Child Health Care Hospital. The aim is to evaluate the impact of a mobile health intervention based on the Behavior Change Wheel theory and Family Health Theory on the prenatal diagnosis rate and pregnancy outcomes of high-risk pregnant women undergoing prenatal screening. The study will be conducted from June 2025 to June 2026. The flowchart of the study is shown in **Figure 3** and **4**.

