#### Standard care group

2.6.2

The standard care group will receive routine prenatal care without the additional mobile health intervention. Routine care includes basic information provided by medical staff at regular checkups, such as prenatal vitamins, ultrasound scans, and general prenatal education.

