### Outcome measures

2.8

There is a total of nine outcomes in the study. Medical staff will use the Questionnaire Star web platform to distribute the questionnaire, and patients will complete the questionnaire online and be instructed by medical staff either in person (at the time of hospitalisation) or by telephone (after discharge). Patient demographic information will be collected through the case system and self-designed questionnaires. (**Table 1**)

**Table 1 T1:** Data collection components and collection timeline.

Type of research	Data collection component	Content	Timepoint	Month 3	After delivery
			Month 0		
Quantitative research	Sociodemographic variables	Sex, age, insurance status, place of residence, average monthly household income, educational level, parents’ education level, area of domicile,	✓		
	Demand for prenatal diagnosis	Willingness for diagnosis, plans for prenatal diagnosis within six months, or having undergone diagnosis	✓	✓	✓
	Pregnancy outcomes	Full-term birth, preterm birth, miscarriage, induced labor due to social factors, and induced labor due to chromosomal abnormalities	✓	✓	✓
	Health Knowledge and Birth Defect Prevention Knowledge Awareness	Self-designed questionnaire	✓	✓	✓
	Obstetric Complications	Gestational hypertension, postpartum hemorrhage, and low-quality infants.	✓	✓	✓
	Depression and anxiety	Patient Health Questionnaire-4 (PHQ-4)	✓	✓	✓
	Decisional Conflict	Decisional Conflict Scale (DCS)	✓	✓	✓
	Self efficacy	Decision Self-Efficacy Scale	✓	✓	✓
	Family Health	Family Health Scale-Short Form (FHS-SF)	✓	✓	✓
	Satisfaction	Decision-making participation satisfaction scale		✓	✓

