This study employs a randomized controlled trial design to assess the effects of personalized mobile health education interventions on prenatal diagnosis participation rates and pregnancy outcomes among high-risk pregnant women. By collecting baseline data from participants, including sociodemographic information and health knowledge, the study aims to deepen our understanding of the factors influencing intervention effectiveness. Based on these data, future intervention strategies could be optimized by tailoring content to better meet the needs of individual participants, thus improving intervention effectiveness and enhancing compliance.

Despite the innovative and practical significance of this study, several limitations require further exploration and resolution in future research. First, the intervention targets only high-risk pregnant women participating in prenatal screening from the Inner Mongolia Maternity and Child Health Care Hospital, with the study sample being limited, which may introduce regional and selection biases. Second, the study primarily relies on self-reported data, which may introduce reporting bias. Additionally, while the study designs an intervention model grounded in the Behavior Change Wheel theory and Family Health Theory, the evaluation of its effectiveness may still be influenced by various factors. For instance, the socio-economic status, cultural background, and family support of the pregnant women may all influence the intervention outcomes. Furthermore, future studies should explore the generalizability of such interventions to low-risk populations, where prenatal diagnosis rates may be constrained by distinct mechanisms.

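### The trial is labelled single-blind, but each participant opens a slip naming her arm and evaluators are unblinded, so no party the protocol names is blinded

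*Protocol article*

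**What the plan says.** Section 2.1 (Design) opens with the label: "This study is a single-blind, interventional randomized controlled trial". The Abstract repeats it. Section 2.4 (Randomization and blinding) explains it: "a single-blind design was adopted, where subjects were unaware of which group they were assigned to, but the evaluators were not blinded". The participant is thus the only party declared blinded.

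Section 2.4 then describes the envelopes. On their content: "A small slip of paper with the group allocation information (Intervention Group and Standard Care Group) was placed inside each envelope". On their use: "Each subject opened their envelope independently to reveal their group assignment". It closes with: "All unused envelopes were securely stored to maintain the integrity of allocation concealment and the single-blind design".

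On the comparator, section 2.6.2 says: "The standard care group will receive routine prenatal care without the additional mobile health intervention".

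**The concern.** The one group said to be blinded is told its allocation by the trial's own procedure. The other group mentioned, the evaluators, is openly unblinded. The design therefore lacks a property that the article states three times.

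The outcomes make this more than a wording matter. Under section 2.8.1 a woman counts as having demand if she answers yes to any one of three items: willingness, plans within six months, or diagnosis already undergone. Only the last is verified. Most secondary outcomes in section 2.8.2 are questionnaires, and obstetric complications are self-reported. The intervention encourages diagnosis throughout and rewards families who complete it (section 2.6.1), so a wish to give the expected answer would act mainly in one direction. A reader who trusts the label would assume that respondents did not know which answer their arm called for.

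**Working it through.** The protocol gives no figure for this point. The core check is a comparison of text, and the arithmetic below only illustrates what could be at stake.

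**Step 1. Who is blinded?**

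| Party | What the document says | Blinded? |
|---|---|---|
| Participant | Said in 2.4 to be unaware; same section has her open a slip naming her arm; arms differ visibly (2.6.1, 2.6.2) | No |
| Evaluators | Stated in 2.4 to be unblinded | No |
| Analyst; those verifying documents or recording pregnancy outcomes | Masking not mentioned, unless they count as evaluators | Not stated |

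The supportable conclusion is that no party the document names is blinded.

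**Step 2. Do the envelopes rescue the label?** No. Sealed opaque envelopes conceal the allocation until it is assigned. Blinding concerns what people know afterwards. Storing unused envelopes may protect the first, but it cannot maintain the second once each woman has read her own slip.

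**Step 3. What could over-reporting do to the demand comparison?**

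Inputs from section 2.3: control demand 34%; 23 per arm before and 29 per arm after the dropout allowance; two-sided α = 0.05.

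Assumptions, not in the document: underlying demand is 34% in both arms; a fraction f of intervention women without demand answers yes; no control woman does so; the test is the uncorrected chi-square.

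Observed intervention proportion = 0.34 + 0.66 × f. The probability of p < 0.05 comes from summing the exact binomial probabilities over all pairs of counts.

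| f | Intervention proportion | 23 per arm | 29 per arm |
|---|---|---|---|
| 0 | 0.340 | 0.0491 | 0.0460 |
| 0.05 | 0.373 | 0.0555 | 0.0530 |
| 0.10 | 0.406 | 0.0743 | 0.0749 |
| 0.20 | 0.472 | 0.1513 | 0.1663 |
| 0.30 | 0.538 | 0.2817 | 0.3222 |

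**Step 4. Sensitivity to the control assumption.** If 10% of control women without demand also answer yes, the control proportion is 0.34 + 0.66 × 0.10 = 0.406. With f = 0.20 the rejection probability then falls to about 0.08 at either sample size.

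The result depends heavily on assumptions that the document cannot settle.

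**The case against.** The contradiction itself has no good answer in the document, but several points limit what can be built on it.

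- **Disclosure.** Section 2.4 openly says evaluators are unblinded, and the Discussion concedes that "the study primarily relies on self-reported data, which may introduce reporting bias". A reported diagnosis is checked against documents or appointment cards. The other primary endpoint, pregnancy outcome, consists of clinical events less open to desirability. All of this stands. However, the limitation never says that respondents know their arm, and the label tells the reader the opposite.
- **Analyst and abstractors.** A reader might infer that these were deliberately left unblinded. The document does not say so. It mentions only evaluators, and analyst masking is often left to an analysis plan, which is not shown here.
- **Questionnaire help.** A reader might infer that staff steer the answers. Section 2.8 says only that patients complete the forms online and will "be instructed by medical staff either in person (at the time of hospitalisation) or by telephone (after discharge"). Instruction in completing a form is not guidance on content, and these staff are not said to be those delivering the intervention.
- **Magnitude.** A reader might take 15% to 32% as this trial's false-positive rate. It is not. Over-reporting of 20% to 30% in one arm only has no source in the document. Demand is defined in 2.8.1 as perceived or expressed need, so a separate true demand is not a quantity the protocol recognises. The bias also comes from self-report in an intervention that could hardly be masked from participants, so correcting the label would not reduce it.

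**Conclusion.** The point holds as a misstatement of the design. By the document's own procedure participants know their arm, evaluators are unblinded, and no other party is named as blinded. This rests on the text alone and needs no assumption. It should be corrected because the label bears directly on how a largely self-reported primary endpoint will be read.

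The size of the resulting bias is not established. For over-reporting of 5% to 30% in the intervention arm alone, the chance of a false significant result on demand is about 5% to 32%. At the low end it is barely above nominal, and it shrinks if control women over-report too. The range shows why the label matters; it does not estimate the error.

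The documents do not support the wider reading that everyone, including the analyst, was left unblinded by choice.

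**What to change.** **Needed, because the text is wrong as written:**

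- Replace single-blind with open-label in the Abstract, 2.1 and 2.4.
- In 2.4, delete the statement that subjects do not know their group and the claim that stored envelopes maintain the single-blind design. Keep the envelopes as a concealment measure.
- Add to the limitations in the Discussion that women answering the self-reported items know their arm.

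**Recommended, at small cost:**

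- Have existing staff who are not told the allocation verify the diagnosis documents and abstract pregnancy outcomes from records.
- Use coded arm labels for the primary analysis.

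If some party is in fact masked, name it in 2.4 instead of leaving the reader to infer it.

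The cost is a few lines of text, a less favourable label and minor reassignment of staff. Sample size, intervention and visit schedule are unaffected. The wording change discloses the self-report bias without removing it. Masked verification and abstraction protect only the document-based outcomes, not the answers on willingness and plans.

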### Theory framework

2.5

#### Behavior change wheel theory

2.5.1

The Behavior Change Wheel theory consists of three levels:

1. **The inner level (source of behavior):** This level focuses on the COM-B model (Capacity, Opportunity, Motivation - Behavior), which identifies the factors that influence the behavior of individuals and helps in recognizing potential behavioral barriers. It aims to explore the sources of target behavior and the underlying causes driving it.2. **The middle level (intervention function)**: This layer develops nine distinct intervention functions, such as education, restriction, and incentivization, which are designed to encourage the formation of the target behavior. These functions can be tailored to the research environment, aiding in the creation of interventions that promote the desired behavior.3. **The outer level (policy categories)**: This level addresses the external factors influencing the interventions, such as laws, regulations, financial incentives, guidelines, communication, service provision, and environmental or social planning. These policy areas assist in shaping the interventions and ensuring the stability of the behavior over time.

The three levels interact and are interrelated, working together to drive the establishment of healthy behaviors in patients for better intervention outcomes. The process of designing an intervention based on this theory typically involves: understanding the behavior (defining the existing problem with behavior-related terminology, selecting the target behavior, describing the behavior in detail, and identifying what can be changed), determining intervention options (choosing intervention functions and policy types), and specifying the content and delivery methods (selecting behavior change techniques and intervention delivery modes).

#### Family health theory

2.5.2

Family health transcends the mere aggregation of individual health statuses and extends beyond traditional definitions confined by blood relationships. It encompasses multidimensional aspects including family structure, interpersonal dynamics, living environments, behavioral patterns, and internal resource allocation. Critically, family health also incorporates external social support systems, particularly access to social networks, healthcare resources, and other societal assets. These intrinsic and extrinsic factors interact reciprocally with individuals, permeating daily life to modify health-related behaviors, awareness, and competencies—thereby collectively shaping the family’s health trajectory. Simultaneously, individual behaviors, perceptions, and capacities reconfigure the relational framework, environmental contexts, and collective actions of the family unit.

The construct of family health emerges through the synergistic interplay between internal family frameworks and externally accessible resources. This paradigm synthesizes key elements from established concepts such as family structure, functional capacity, and social connectivity, while enhancing a family’s ability to mobilize external resources and strengthen societal engagement. By emphasizing health-relevant determinants, it establishes an integrative nexus between individual well-being and population health outcomes. Such conceptualization provides a robust foundation for investigating health disparities and designing family-centric interventions within public health research.

#### Combination of behavior change wheel theory and family health theory

2.5.3

The convergence of the Behavior Change Wheel (BCW) framework and Family Health Theory offers a transformative paradigm for designing health behavior interventions, particularly salient in contexts where the family unit constitutes the fundamental societal building block. By integrating the BCW’s emphasis on environmental determinants, the COM-B model (Capability, Opportunity, Motivation-Behavior), and targeted intervention functions with Family Health Theory’s focus on intrafamilial interactions, resource mobilization, and external support systems, this synthesis facilitates the development of multidimensional intervention strategies. Such strategies holistically address both individual-level behavioral drivers and family-level systemic dynamics, thereby optimizing health behavior modification across micro and macro units of analysis.

This interdisciplinary approach enables the creation of context-sensitive interventions that leverage familial cohesion as a catalyst for sustainable behavioral change. Specifically, the BCW’s systematic mapping of behavior change techniques aligns with Family Health Theory’s emphasis on resource accessibility and social embeddedness, allowing researchers to operationalize interventions that simultaneously strengthen family health capital and enhance individual COM-B components. The resultant framework provides a novel theoretical scaffold for investigating how family-mediated interventions can amplify the efficacy of traditional behavior change models while addressing health disparities rooted in familial and social contexts.

### Intervention

2.6

This study established a multidisciplinary team consisting of genetic experts, nursing specialists, genetic doctors, and public health experts. Through several rounds of in-depth discussions, team members combined their expertise to develop comprehensive intervention strategies aimed at addressing the behavioral barriers to prenatal diagnosis participation among high-risk pregnant women, incorporating mobile health technology as a key tool.

#### Intervention group

2.6.1

The intervention program combines the Behavior Change Wheel (BCW) theory and Family Health Theory, with a particular emphasis on helping high-risk pregnant women overcome negative emotions such as anxiety and depression through family support systems, ultimately improving pregnancy outcomes and increasing prenatal diagnosis rates (**Figure 6**). The intervention will last for 12 weeks, during which the WeChat platform will be used consistently to deliver continuous health education, emotional support, and behavioral feedback. The goal is to help pregnant women overcome emotional barriers and increase their participation in prenatal diagnosis and improve their pregnancy outcomes through emotional management, behavioral support, and family involvement.

**Figure 6 f6:**
[figure not shown]
Combination of behavior change wheel theory and family health theory.

**Step 1: Understanding behavioral issues (based on COM-B model and family health integration analysis)**

Using the BCW's Capability, Opportunity, Motivation-Behavior (COM-B) model and integrating family health factors, this step will thoroughly analyze the behavioral barriers to high-risk pregnant women participating in prenatal diagnosis.

**Target behavior:** The target behavior is to enhance the awareness of high-risk pregnant women and their families regarding prenatal diagnosis, promote joint participation by the pregnant women and their partners, and help families correctly interpret the diagnosis results. Additionally, emotional management and psychological support will be provided to reduce anxiety and depression, improving pregnancy outcomes.
**Behavioral barrier analysis (integrating family health factors):**

**Capability:**
▪ **Psychological capability:** High-risk pregnant women and their family members (especially husbands) often have limited knowledge about prenatal diagnosis, its processes, and its importance. Cognitive gaps within the family may lead to inconsistent decisions or lack of support. Providing easy-to-understand educational materials for families and emphasizing joint participation in health decision-making can address these gaps. Additionally, high-risk pregnant women often experience anxiety and depression, which can affect their decision-making and behavior. Emotional support and psychological interventions will help manage these emotions and increase their participation in prenatal diagnosis.▪ **Physical capability:** Pregnant women’s physical conditions, such as pregnancy symptoms, anxiety, or concerns, may affect their participation in diagnosis. Providing emotional comfort and emotional support from family members can help alleviate these issues. Support from husbands and other family members can enhance the pregnant women’s willingness to participate in and complete the diagnosis.
